## Abstract

**Background:**

Dental caries (tooth decay) is highly prevalent and is largely attributable to unhealthy self-care behaviors (diet and oral hygiene). The conventional (health) education (CE), focusing on disseminating information and giving normative advice, often fails to achieve sustained behavioral changes. This study incorporates two innovative elements into CE: (i) motivational interviewing (MI), a client-centered counseling for changing behaviors, and (ii) an interactive caries risk assessment (RA) tool, which is devised to facilitate dental counseling and may enhance MI in several ways. Through a randomized, controlled, evaluator-blinded trial, three intervention schemes (CE, CE + MI, and CE + MI + RA) will be compared for their effectiveness in eliciting dentally healthy behaviors and preventing caries in preschool children.

**Methods/Design:**

This study targets 3-year-old children who are at a critical stage for embedding health habits. Children with unfavorable dental behaviors (insufficient toothbrushing and/or frequent snacking) and their parents will be recruited from 12 participating kindergartens. Parent-child dyads (n = 690) will be randomly assigned into three groups. In the first group (CE), oral health information and advice will be delivered to parents through pamphlets. In the second group (CE + MI), in addition to the pamphlets, individual MI counseling with each parent will be performed by one of two trained dental hygienists. In the third group (CE + MI + RA), besides pamphlets and MI, interactive RA will be integrated into MI to motivate parents and facilitate their informed decision making and goal planning. At baseline and after 12 and 24 months, parents will complete a questionnaire and children will undergo a dental examination. The effectiveness of the intervention schemes will be compared over 12 and 24 months. The primary outcome will be caries increment in children and proportion of caries-free children. Secondary outcomes will be changes in parental efficacy for protecting children’s oral health and changes in children’s dental behaviors.

**Discussion:**

Motivating and empowering parents to cultivate dentally healthy habits of young children presents both promises and challenges. With careful methodological considerations, this study is expected to provide scientific evidence for public health workers, dentists, and dental auxiliaries (nurses and hygienists) to choose appropriate interventions to advance children’s oral health.

**Trial registration:**

HKCTR-1455

## Background

Dental caries (tooth decay) is one of the most common oral diseases. As estimated by the World Health Organization (WHO), 5 billion people of the world’s 6.5 billion population are affected by dental caries [1]. The onset of dental caries can start soon after an infant's teeth erupt. The presence of one or more decayed, missing (due to caries), or filled tooth surfaces in any primary tooth in a child 71 months of age or younger is defined as early childhood caries (ECC) [2]. In the USA, caries is the most common chronic childhood disease, five times more prevalent than asthma, afflicting 30% of children aged 2 to 5 years [3]. In Hong Kong, 50% of children suffer from caries at the age of 5 years [4]. ECC imposes significant threats to the physical, psychological and social well-being of young children, constitutes a heavy financial burden on society, and, if not treated promptly and properly, may cause lethal systemic infections [5,6]. Recent life-course studies have linked ECC to subsequent caries in permanent dentitions [7,8], indicating a lifetime impact of ECC on one’s health.

Like many other chronic diseases, dental caries is a multifactorial disease highly determined by one’s ‘lifestyles’ [9,10]. It is preventable by adopting healthy behaviors, such as regular toothbrushing, favorable dietary habits and regular dental check-up. Promoting dentally healthy lifestyles is identified by the WHO as a priority and strategic orientation for oral health promotion [11]. Since early childhood is a critical stage for forming health habits, and parents are often receptive at this stage [12], this period offers a unique opportunity for behavioral interventions. Cultivating dentally healthy habits among preschool children, whose permanent teeth will later erupt, would maximize the chance of a caries-free permanent dentition throughout a lifetime [2].

Conventionally, health education focuses on disseminating information and giving normative advice. The insufficiency of conventional (health) education (CE) has been documented [13]. Although dental knowledge can almost always be improved by CE, such knowledge gain does not translate into sustained changes in dental behaviors [13]. A typical CE session is often an exercise in overt persuasion. However, what appears to be a convincing line of reasoning to the dental professional falls on deaf ears or result in reluctance to change [14]. The fruitless efforts of CE have led initially enthusiastic dental professionals to a state of burnout and created skepticism toward such attempts [14,15].

To address the limitations of CE, motivational interviewing (MI) was developed as an interventional style. Evolving from Rogers’ person-centered counseling approach and embracing the transtheoretical theory, MI elicits clients’ intrinsic motivations, enhances their readiness to change, and helps to explore and resolve ambivalence [16]. Clients assess their own behaviors, present arguments for change and decide what behavior, if any, to focus on, while the counselor helps to create, by skilful questioning and reflection, an acceptable resolution that triggers change [17]. Such a client-centered approach is in clear contrast to the traditional health education and counseling in which professionals are the most active participants in presenting problems and offering solutions, while clients are normally excluded from problem definition and decision-making [17,18].

MI was first applied to tackle the most difficult-to-change behaviors - substance abuse - and was later used to treat a broad range of lifestyle problems, such as eating disorder, lack of physical exercise, and poor adherence to medication regimens. Its treatment effect ranged from 0.25 to 0.57 across studies [19]. A systematic review has shown that, in 60% of 29 randomized trials, MI yielded at least one significant behavioral change [20]. MI did not emerge in dental research until recent years. In a South Asian immigrant community in Canada, a dental MI intervention that focused on modifying mothers’ infant-rearing practices was found to be effective in reducing the caries increment in infants (6 to 18 months of age) over 2 years (hazard ratio = 0.54, 95% confidence interval = 0.35 to 0.84) [15,21]. Nevertheless, in a recent study among low-income African Americans, MI with caregivers showed no significant effect on children’s dietary habits and caries increment; only marginal improvement was seen in their oral hygiene measures which, however, declined over 2 years [22]. The limited number of dental MI studies and their contradictory findings point to the need for further investigations involving a breadth of populations for understanding the role of MI in improving children’s oral health.

To maximize the potential of MI, some tools can be incorporated to facilitate the MI counseling. In the dental context, a potentially useful tool to assist MI counseling is an interactive caries risk assessment (RA) program called Cariogram [23]. Enhanced with artificial intelligence, this computer program generates a pie diagram that analyses one’s caries risk in a manner understandable to lay persons. The overall risk is quantified and broken down into various causes, such as diet and oral hygiene. In contrast to a standard list of do’s and don’ts prescribed to all, Cariogram pinpoints the most needed behavioral change(s) to a specific client, while allowing alternative options. The dental counselor can discuss with the client about various possible behavioral changes, whose expected health gains (risk reduction) can be demonstrated interactively (Figure 1).

**Figure 1 F1:**
[figure not shown]
A case exemplifying the interactive risk assessment (Current risk and risk reduction through various behavioral changes are demonstrated).

This interactive RA program may facilitate MI in several ways: (1) help to establish rapport and bring the client into a meaningful conversation; (2) assist the client’s systematic reflection on and appraisal of his/her dental habits; (3) motivate the client by demonstrating his/her caries risk and health gains achievable through behavioral changes; (4) pinpoint target behavior(s) and offer alternative solutions; (5) allow stepwise improvement and enhance self-efficacy; and (6) facilitate better informed decision-making and assist the client to set his/her own goal and agenda. Theoretically, this interactive RA program may enhance the effectiveness of MI in changing dental behaviors. This assumption, however, is yet to be empirically tested.

This study, through a randomized controlled trial, aimed to evaluate and compare the effectiveness of three intervention schemes (CE, CE + MI, and CE + MI + RA) in enhancing parental efficacy for protecting children’s oral health, improving preschool children’s dental behaviors, and preventing early childhood caries. The null hypothesis is: There is no difference among these three groups in parental efficacy, children’s dental behaviors, and caries increment among children.

## Methods/Design

### Sample size calculation

The main outcome of this study will be any caries increment or not (change in decayed, missing, and filled teeth (△dmft >0 or = 0) in the study children. Our latest survey showed that about 35% of Hong Kong children aged 3 years develop new caries in one or more teeth (△dmft >0) in a year [24]. An intervention will be considered to have a clinically significant effect if it reduces this rate to 20% in a year. Such a magnitude of effect size (relative risk of 0.57) was also reported by a previous MI trial in infants [15]. In order to detect such a reduction at a significance level of 5% and a statistical power of 80%, 184 parent-child dyads per group will be needed (multiple comparisons considered). Allowing for a 20% attrition rate, 230 parent-child dyads would need to be recruited into each of the three study groups. The total sample size will be 690.

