### Statistical analysis

Participants in the three intervention groups will be compared on their demographic background (age and gender), family socioeconomic status (parental education and family income), and baseline oral health behaviors and tooth status. The effectiveness of the intervention schemes will be evaluated and compared over 12 and 24 months through an intention-to-treat analysis, in which participants will remain in their originally assigned group regardless of the intervention actually received and subsequent withdrawal or deviation from the original intervention protocol [31]. For those who are lost to follow-up, the last assessment made will be considered valid throughout the study period.

The primary outcome will be caries increment in children and the proportion of caries-free children, measured by the number of new carious teeth (△dmft; continuous variable) and whether there are any new carious teeth (△dmft >0 or = 0; dichotomous variable). Secondary outcomes will be changes in parental efficacy in protecting children’s oral health and changes in children’s dental behaviors (outcome variables described in Table 2). Effect sizes (relative risk) and their confidence intervals will be calculated. Chi-square tests will be used for comparing proportions; means will be compared through parametric or non-parametric methods, as appropriate. Number needed to treat, calculated as 100 divided by the risk difference expressed as a percentage [32], will be presented to provide an estimate of the number of parents needed to be counseled in order to avoid one child with new dental caries.

**Table 2 T2:** Outcome variables

**Outcomes**	**Variables**	**Codes**	**Source of information**

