**PRIMARY OUTCOME**			
**Caries increment in child***			
	Number of new carious teeth (△dmft)	Continuous	Dental examination
	Any new carious teeth (△dmft >0 or = 0)	Dichotomous	Dental examination
**Caries free child**	dmft = 0 or >0	Dichotomous	Dental examination

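### The sample size rests on one binary outcome over one year, but the analysis labels several variables primary at 12 and 24 months and names none as deciding

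*Protocol article*

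**What the plan says.** The protocol article's section on sample size calculation names one endpoint: "The main outcome of this study will be any caries increment or not", that is, △dmft >0 or = 0. The control rate is that "about 35% of Hong Kong children aged 3 years develop new caries in one or more teeth" in a year, and an intervention counts as clinically significant "if it reduces this rate to 20% in a year". The calculation is made "at a significance level of 5% and a statistical power of 80"%, gives 184 dyads per group, and notes in parentheses that multiple comparisons were considered. It does not say how many comparisons or which method.

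The statistical analysis section defines the endpoint differently: "The primary outcome will be caries increment in children and the proportion of caries-free children". Effectiveness "will be evaluated and compared over 12 and 24 months through an intention-to-treat analysis". Table 2 lists three variables under the primary heading: the number of new carious teeth (continuous), any new carious teeth (dichotomous), and "Caries free child" (dmft = 0 or >0). The abstract also gives caries increment plus the proportion caries-free, compared over 12 and 24 months.

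None of these later places repeats that any new caries is the main outcome, says which visit decides, or says how the primary variables combine into a conclusion.

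**The concern.** The two descriptions cannot both define the primary outcome. The sample size allows for multiplicity on one variable over one year. The analysis gives primary status to up to three variables at two visits.

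The three variables overlap but are not the same variable restated. Randomization is stratified by baseline dmft = 0 or >0, so children who already have caries are enrolled. Such a child can develop no new caries and still not be caries-free.

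As the text stands, the variable and visit that carry the conclusion could be chosen after the data are seen. The 5% used to size the trial would then not be the error rate of the trial's primary claim.

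**Working it through.** **Inputs from the article:** rates 0.35 and 0.20 in one year; significance level 5%; power 80%; 184 per group; 20% attrition; three arms at 1:1:1. Two-sided testing is assumed, because sidedness is not stated ("Chi-square tests will be used for comparing proportions").

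**Step 1: reproduce 184.** Two proportions, pooled variance under the null, no continuity correction:

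n = [z(1−α/2)·√(2p̄(1−p̄)) + z(0.80)·√(p₁(1−p₁)+p₂(1−p₂))]² / (p₁−p₂)²

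Here p̄ = 0.275, √(2p̄(1−p̄)) = 0.6315, √(0.2275+0.16) = 0.6225 and z(0.80) = 0.8416.

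| α per comparison | z | n per group |
|---|---|---|
| 0.05 | 1.960 | 137.9 |
| 0.05/2 | 2.241 | 167.1 |
| 0.05/3 (Bonferroni) | 2.394 | 184.2 |
| 1−0.95^(1/3) = 0.01695 (Šidák) | 2.388 | 183.5 |

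Šidák for three comparisons rounds up to exactly 184, and Bonferroni rounds up to 185. Two comparisons with a continuity correction give 181, which is close. On any of these readings the correction covers arm comparisons of one variable at one visit. Attrition: 184/(1−0.20) = 230, and 3 × 230 = 690. The arithmetic is sound.

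**Step 2: count the primary comparisons if every listed variable and visit is tested pairwise.** 3 variables × 2 visits × 3 pairs = 18. This count is inferred; the article does not state it.

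**Step 3: upper limits on the family-wise error at 0.05/3 per test.**

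| Family | Tests | Bonferroni sum | If independent, 1−(1−0.05/3)^k |
|---|---|---|---|
| One variable, one visit | 3 | 5% | 4.9% |
| One variable, two visits | 6 | 10% | 9.6% |
| Three variables, one visit | 9 | 15% | 14.0% |
| Three variables, two visits | 18 | 30% | 26.1% |

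The tests are positively related, so the true figures for the larger families lie below these.

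**Step 4: allow for correlation by simulation under no effect.** One run used 184 per group, 4,000 trials per setting, gamma-Poisson increments and 35% one-year incidence. Baseline caries was set at 0%, 25% or 40%, with a doubled rate in affected children. The increment model and the baseline caries levels are assumptions. At 0.05/3 per test:

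| Family | Chance of at least one significant result |
|---|---|
| One variable, one visit | 4-5% |
| One variable, two visits | 7-9% |
| Three variables, one visit | 7-11% |
| All 18 | 11-17% |

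Other runs with different assumptions about dispersion and baseline caries gave about 7-13% for all 18. The range to quote is therefore roughly 7-17%. With 0.05 per test and no correction, the runs gave about 20-30%.

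**Step 5: what splitting α would cost instead (35% vs 20%, Bonferroni).**

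| Split | Power at 184 | n per group for 80% | With attrition | Total |
|---|---|---|---|---|
| 0.05/6 | 72% | 214 | 268 | 804 |
| 0.05/9 | 68% | 231 | 289 | 867 |
| 0.05/18 | 59% | 259 | 324 | 972 |

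**Step 6: power if 24 months were the single primary visit** (184 per group, α = 0.05/3, years independent). The control rate is 1−0.65² = 57.8%.

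- Full effect in both years: 1−0.80² = 36.0%, power about 97%.
- No effect in year 2: 1−0.80×0.65 = 48.0%, power about 30%.

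**The case against.** The article does have a lead outcome. The sample size section names it, and the number needed to treat is framed around the same event, a child with new caries. On this view Table 2 merely fails to repeat the label, and testing order and adjustment method may stand in an analysis plan that is not shown. The null hypothesis is worded as no difference among three groups, so one three-group test per variable and visit may be meant rather than pairs. Nothing in the article says that any one significant result counts as success.

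Much of this stands. It rules out treating 18 tests, or any single error rate, as a fact about the trial. It does not remove the contradiction: one section has one main outcome, while three other places give primary status to more than one variable and to neither visit in particular. An unseen plan may supply testing detail, but it does not make these statements agree. Reading the tests as three-group comparisons does not restore 5% either: six such tests at 0.05 gave 8-12% in null simulations.

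A reader might also infer that 690 is too small. The documents do not support that: 184, 230 and 690 are correct for the outcome they were computed for.

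**Conclusion.** The point holds: the primary outcome is defined inconsistently, and the correction that fits 184 per group covers one variable at one visit. If a significant result on any listed primary variable at either visit counts as success, the family-wise error is roughly 7-17% at 0.05/3 per test, or about 20-30% uncorrected, against the stated 5%.

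This rests on three assumptions. The any-result-counts rule is neither stated nor excluded. Three comparisons is inferred from the match to 184. The size of the inflation depends on baseline caries and correlation, which the article does not give.

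A reader might conclude that moving the primary visit to 24 months would secure about 97% power. That needs the full yearly effect to persist through year 2, whereas the scheduled counselling contacts in Table 1 end at 6 months. With no year-2 effect, power is about 30%.

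**What to change.** In the abstract, the sample size section, the statistical analysis section and Table 2, name one primary outcome: any new carious tooth (△dmft >0) from baseline to 12 months. Test it with the three pairwise comparisons, corrected as in the sample size, and state the number of comparisons and the method. Make the △dmft count, caries-free status and all 24-month results secondary. The figures 184, 230 and 690 then need no change.

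If the sponsor prefers 24 months as the single primary visit, restate the power as a range that shows both the 97% and the 30% case and the assumption behind each.

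The trial status section says that recruitment has not begun, so the cost now is mainly wording, plus a check that the registered outcome agrees. The real downside is that the other outcomes lose confirmatory status.

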### Recruitment and randomization

The protocol of this study has been reviewed by the Institutional Review Board of University of Hong Kong⁄Hospital Authority Hong Kong West Cluster. An ethical approval was obtained (#UW 11-483). This study involves parent-child dyads. Informed written consent will be obtained from each participating parent.

To be eligible to join this study, a child should be (a) enrolled in kindergarten Grade 1 (K1), (b) aged 3 years, and (c) having unfavorable oral health behavior(s) (that is, a child who needs intervention). Unfavorable oral health behaviors are defined as “brush teeth less often than twice a day” and/or “snack three times or more a day”. Each child will be required to join this study together with his/her parent (mother or father) who spends the most time with him/her, so that a parent-child dyad can be recruited. A child will be excluded if (i) he/she has a serious medical condition or (ii) his/her parents are non-Chinese speaking and cannot understand the oral health materials and counseling, which will be in Chinese.

A screening questionnaire will be used to identify participants who fulfil the above-mentioned criteria. According to our latest survey in Hong Kong [24], 60% of children aged 3 years have unfavorable oral health behaviors (24% with insufficient toothbrushing only; 26% with frequent snacking only; and 10% with both). To reach the target number of 690 parent-child dyads (230 dyads in each of the three groups), 1,150 children would need to be screened (1,150 × 60% = 690). Considering an average number of 120 children in K1 of a kindergarten and an estimated response rate of 80% (based on our recent experience), 12 participating kindergartens will need to be recruited (120 × 80% × 12 = 1,152).

A research nurse will review the screening questionnaire and recruit all eligible parent-child dyads who agree to participate. After baseline data collection, participants in each kindergarten will be randomly assigned into three groups (1, CE; 2, CE + MI; and 3, CE + MI + RA) by a research assistant not involved in the enrolment of the participants, delivery of intervention, or data collection. The randomization will be stratified by parental education (“secondary education or below” or “tertiary education”) and child’s caries experience at baseline (“dmft = 0” or “dmft >0”), which are perceived important confounders in this study. For each stratum, to ensure an equal number of subjects in each group (that is, an allocation ratio 1:1:1), a block randomization will be performed (block size of 6). A computerized random sequence generator will determine intervention status of the subjects. Intervention status is then placed into a sequentially numbered envelope for each group and each envelope is sealed and opened before the delivery of intervention so that allocation concealment can be achieved.

### Oral health assessment

All participants will be assessed at baseline and followed-up after 12 and 24 months, so that the outcomes of the interventions can be determined.

A questionnaire (in Chinese) pre-tested in our previous study [24] will be completed by parents to gather information on (i) family socio-demographic background, (ii) parental knowledge of and attitudes toward oral health, (iii) parental efficacy in protecting the child’s oral health, (iv) child’s oral health behaviors (diet and oral hygiene), and (v) child’s history of dental treatment and use of caries-preventive agents, such as topical fluorides.

All child participants will undergo a dental examination. The examiner has been trained regarding the diagnostic criteria and examination methods and will be further calibrated against an experienced oral epidemiologist to ensure an agreement rate over 90%. Duplicate examinations will be carried out on 10% of the subjects, for assessing the intra-examiner reliability. Each child will be examined in the supine position. A mouth mirror, illuminated by an intra-oral LED light, and a community periodontal index (CPI) probe will be used. The status of each tooth surface will be assessed by visual inspection, aided by tactile inspection if necessary. No radiographs will be taken. The WHO recommended diagnostic criteria for dental caries will be followed - that is, caries will be recorded as present when a lesion in a pit or fissure, or on a smooth tooth surface, has an unmistakable cavity, undermined enamel, or a detectably softened floor or wall [25].

The oral hygiene status will be evaluated using the Silness-Löe Plaque Index [26]. The examiner will be blinded to the group allocation of each child subject throughout the whole study.

